## Abstract

**Background:**

Investing in mental well-being is considered a supplement to current mental health service delivery in which the treatment and prevention of mental disorders are core components. It may be possible for people to enhance their well-being by boosting their “mental fitness.”

**Objective:**

Psyfit, an online, multi-component, fully automated self-help intervention, was developed with the aim of improving well-being and reducing depressive symptoms. The efficacy and cost-effectiveness of this intervention will be examined in a randomized controlled trial.

**Methods:**

In this two-armed randomized controlled trial, a total of 290 participants will be assigned to use Psyfit (experimental condition) or to a 6-month waiting list (control condition). Adults with mild to moderate depressive symptoms interested in improving their mental fitness will be recruited from the general population through advertisements on the Internet and in newspapers. Online measurements by self-assessment will be made prior to randomization (pre-test), 2 months after baseline (post-test), and 6 months after baseline (follow-up).

**Results:**

The primary outcome is well-being. Secondary outcomes are depressive symptoms, general health, vitality, and economic costs. Analysis will be conducted in accordance with the intention-to-treat principle.

**Conclusions:**

This study will examine the efficacy and cost-effectiveness of an online intervention that aims to promote well-being in people with elevated levels of depressive symptoms. If shown to be effective, the intervention could prove to be an affordable and widely accessible intervention to improve well-being in the general population.

**Trial Registration:**

The study is registered with the Netherlands Trial Register, part of the Dutch Cochrane Centre (NTR2126).

## Introduction

Depression, anxiety disorders, and alcohol dependency are highly prevalent mental disorders [1,2] and among the 10 disorders with the greatest disease burden [3]. These disorders are associated with reduced quality of life [4] and high economic costs due to productivity losses and high levels of health service uptake [5]. In addition, many more people suffer from poor well-being [6], subclinical depression [7], and stress at work [8] putting them at greater risk of developing a mental disorder later on. In the current dynamic and innovative knowledge- and service-driven economy, more people are faced with mentally demanding jobs. This places unique demands on people’s emotional, social, and cognitive capacities [9,10]. Countries are challenged by the adverse consequences stemming from these demanding circumstances, such as burnout, absenteeism, and subsequent economic costs. Therefore, it is important is to reach people at an early stage when the development of a full-blown mental disorder might still be prevented. So far, preventive interventions developed for this reason focus mainly on the prevention of mental health problems and disorders, and less on the improvement of well-being [11].

The World Health Organization (WHO) defines mental health as “a state of well-being in which the individual realizes his or her own abilities, can cope with the normal stresses of life, can work productively, and is able to make a contribution to his or her community.” This definition of mental health represents a paradigm shift from focusing on the narrow medical constructs of illness and disease only, to embracing well-being as well [12].

The WHO definition also underscores the notion that mental health is not merely the absence of mental illness. Well-being and mental illness, although correlated, are independent concepts and not just opposites on a single continuum. People presenting with low levels of well-being have similarly poor psychosocial outcomes as people suffering from mental illness [13]. Likewise, people with mental disorders are capable of experiencing well-being, to some degree [14]. In general, people with high levels of well-being are physically healthier, live longer, are more productive at work, and use less health care [15,16]. Longitudinal and experimental evidence suggests that positive affect and well-being may generate these desirable outcomes [17]. The available evidence suggests that the enhancement of well-being might be a valuable public health strategy in mental health promotion.

With this positive approach to mental health in mind, we developed an Internet-based self-help intervention (“Psyfit”) aimed at the promotion of well-being. Below, we elaborate on the public health rationale for this type of intervention, including the definition of well-being, the relevance of the Internet as an implementation vehicle, and the use of positive psychology interventions as a starting point.

### Definition of Well-being

There are three different types, or concepts, of well-being. The first is subjective well-being, which is a cognitive and/or affective appraisal of one’s own life as a whole and seeking a balance between positive and negative emotions [18]. The second is the concept of psychological well-being. This concept builds on the work of Carol Ryff who was dissatisfied with the emphasis on subjective well-being and focused more on the optimal functioning of the individual [19]. In Ryff’s view, psychological well-being contains six elements: self-acceptance, autonomy, environmental mastery, personal growth, purpose in life, and personal relations with others. According to this view, the attainment of personal happiness is not the goal in life, but rather self-actualization and meaning. The third concept arose from the work of Corey Keyes who called for a broader and less self-centered orientation towards well-being and for the expansion of subjective and psychological well-being to include social well-being; in other words, a complete state model of mental health [6]. Social well-being refers to the extent to which a person feels at home in society, trusts other people, and makes sense out of the world. The WHO’s definition is clearly rooted in this perspective.

### Using the Internet: eHealth

The promotion of well-being requires the delivery of effective and accessible interventions aimed at sustainable behavioral change. The Internet might offer the opportunity to reach this goal. Using persuasive technology techniques, programs designed to change attitudes and behaviors can be made for computers, game systems, and mobile devices [20] so that they are highly engaging and enjoyable at the same time. Internet interventions are defined as highly structured; self- or semi self-guided; founded on evidence-based, face-to-face interventions; tailored to provide follow-up and feedback; personalized to the user; interactive; and enhanced by animation, audio, or video technology (if possible) [21].

eMental Health interventions can vary from plain information, tailored advice, single exercises, and interactive self-help programs to structured online therapies with or without guidance from a therapist. The major advantages of eMental Health are that Internet interventions can be offered on a broad scale, they are able to engage hard-to-reach people, and they can reduce therapists’ time (ie, reduce costs) [22].

In the field of Internet interventions, the efficacy of interventions aimed at the reduction of depressive symptoms or anxiety has been demonstrated meta-analytically [23]. The majority of these programs are based on cognitive behavioral therapy [24] and problem-solving therapy [25,26].

### Positive Psychology Interventions

The positive psychology movement has developed many interventions that focus on flourishing and positive functioning. These include counting one’s blessings [27-29], practicing kindness [30,31], setting personal goals [32-34], expressing gratitude [28,29], and using personal strengths [28]. A comprehensive meta-analysis of 51 positive psychology interventions has demonstrated moderate effect sizes for enhancing well-being and reducing depressive symptoms [35].

However, experimental research on well-being interventions offered over the Internet is still scarce and the results are mixed. A randomized controlled trial with 2 separate interventions (working with your strengths and problem solving) and a placebo control group showed mixed results [36]. Well-being was improved, but there was not a significant impact on mental illness. In another trial [28], the Internet was used for the recruitment of participants and the collection of data. The single exercises (using signature strengths in a new way and recapitulating three good things) enhanced well-being and reduced depressive symptoms for up to 6 months. Also, “writing and reading a gratitude letter” was effective, but only in the short term. However, a more critical look at the interventions reveals that these exercises were not truly Internet-based interventions as described in the previously cited definition by Ritterband [21] because the interventions were neither interactive nor personalized. Another two randomized controlled trials examined the effects of multi-component interventions [37, 38]. In a workplace setting, an intervention called “Resilience Online” did not demonstrate any significant effects [37]. In another study using an online version of positive psychotherapy, depressive symptoms were significantly reduced, but there was no improvement in subjective well-being [38].

### The Current Study

The aim of this study is to evaluate the efficacy and cost-effectiveness of Psyfit, an online well-being program [39]. The study will add to the existing literature by testing a multi-component and flexible Internet-based intervention to promote well-being. To date, the research in this area is limited to either single interventions focusing on one well-being exercise at a time [28, 36] or to multiple protocol-based interventions [37,38]. In these studies, participants in the intervention groups are allocated to an inflexible intervention, although most people would prefer to choose what they need and feel up to doing [30,40,41]. For this reason, Psyfit offers a choice of different interventions that participants can tailor themselves.

The primary objective of this study is to evaluate the effectiveness of the Psyfit intervention in comparison to a waiting list control group. We hypothesize that the intervention group will demonstrate a significant increase in well-being and a reduction in depressive symptoms at post-test and follow-up compared to the control group. Secondary study objectives are to conduct an economic evaluation and to examine if particular subgroups benefit differently (ie, more or less) than others from the intervention.

## Methods

### Study Design

This study is designed as a randomized trial with two parallel groups. In the experimental condition, participants will receive 2 months free access to Psyfit. In the control condition, participants will be put on a waiting list for 6 months before they are offered access to Psyfit. The study is designed to compare the efficacy and cost-effectiveness of Psyfit relative to the waiting list control condition. A secondary objective is to examine whether certain groups (eg, based on depressive symptoms, gender, and education level) benefit differently from the intervention. Participants in both conditions will have unrestricted access to professional help, if needed. The study protocol, interventions, participant information, and informed consent procedure have been approved by the Dutch Medical Ethics Committee for Mental Health Care (METIGG), under registration number 9218.

### Inclusion and Exclusion Criteria

The participant group is defined as everyone willing to improve their “mental fitness.”

Participants will be included if they: (1) are 21 years or older; (2) present with very mild to moderate depressive symptoms with a score between 10-24 on the Center for Epidemiological Studies Depression Scale (CES-D); (3) have moderate or low levels of well-being as measured with the Mental Health Continuum-Short Form (MHC-SF); (4) have access to a computer and the Internet; and (5) have sufficient knowledge of the Dutch language. The CES-D [42] and MHC-SF [43,44] inclusion and exclusion scores are based on established cut-off points.

People with serious depressive symptoms (CES-D score =>25) or active suicidal thoughts or plans (determined from the Web Screening Questionnaire [45]) will be excluded from this study. Those who fail to meet these selection criteria will be notified by email and will be advised to contact their general practitioner if their depressive symptoms exceed the threshold limit. In cases of suicidal ideation, people will be urgently referred to the national online suicide-prevention platform for help.

### Recruitment

Participants will be recruited through banners on Internet websites related to mental health and well-being. In addition, advertisements will be placed in newspapers and monthly magazines on health-related topics.

The recruitment message for the study is formulated positively (ie, not with a focus on symptoms and problems): “Would you like to increase your mental fitness? Would you like to feel better? Improve your mental fitness and participate in our study of an online self-help program, Psyfit.” The analogy is made with physical fitness: “There are certain lifestyle behaviors you could adopt that can make you feel mentally fit.” Preliminary focus group research has shown that people with minor mental health problems, those experiencing stress, or those who just “don’t feel good” are attracted by the “mental fitness” message [46].

The advertisements will include the website address where people can register for Psyfit (www.psyfit.nl). This website contains complete information about the study and a demonstration video of the intervention. Those interested in participating can leave their name and email address. The email and Internet Protocol (IP) addresses will be checked for multiple registrations. Following this, prospective participants will receive an email with additional information about the study and a link to the online informed consent form and online questionnaire.

### Randomization

The online randomization procedure will be carried out at the individual level. After returning the informed consent form and completing the baseline questionnaire, people who meet the inclusion criteria will be randomly allocated to the experimental group (Psyfit) or to the waiting list and they will be notified by email. Randomization will be stratified by gender, education, and severity of symptoms based on CES-D scores (scores between 10-15 and 16-24). A computer program will allocate participants using a generated randomization list. Block randomization in blocks of two will be performed to ensure equal distribution of participants across conditions.

### Intervention Group: Psyfit

Psyfit is offered as an online and fully automated self-help intervention without active support from a therapist (see Figure 1 for a screenshot of the intervention). Participants tailor their own intervention program to their personal needs and measure their progress by several self-tests. In addition, they can discuss their experiences in an online community accessed via Psyfit.

The content of the well-being program, Psyfit, is based on an extensive literature review [10]. Elements in the intervention originate from positive psychology [28,35], mindfulness [47], cognitive behavioral therapy [48], and problem-solving therapy [49].

Psyfit consists of six modules, each containing a 4-week program:

1. Mission and goals (living from a deeply felt mission and personal values);

2. Positive feelings (positive thinking and working on your positive affect);

3. Positive relations (connection with other people and your environment);

4. Living in the moment (consciously living and enjoying);

5. Thinking and feeling (change negative thinking patterns, optimistic thinking); and

6. Master your life (managing personal energy, stress, and problems).

In theory, each module is likely to have impact on well-being. During the study, the Psyfit website is accessible only to the participants in the experimental group. An email will be sent to each participant assigned to Psyfit with a personal username and password. From the moment the participant logs on, a 2-month free access to the intervention is activated. If a participant doesn’t log on, a reminder email with the log-on codes will be sent after one week and, if necessary, after two weeks and again after three weeks. Participants are allowed to use the program at any time they want during the trial period. Participants are advised to choose and finish at least one module during the intervention period. During each 4-week module, participants receive background information on the specific subject, view short films, and receive a weekly assignment that they are expected to complete during that week. On average, this takes 20 to 30 minutes each day.

Participants are free to use all other functionalities offered in Psyfit and can always choose to start a new module. For an overview of functionalities, see Textbox 1.

 Functionalities in PsyfitGeneral self-test to assess individual well-being level beforehand and after 2 months.A personal plan in which the participant can reflect on his or her goals, motives, and pitfalls.A “mood meter” for monitoring changes in the mood of the participant. The outcomes are presented in a graph.Automatic email service twice a week with reminders, tips, and advice.Online community for sharing experiences and peer-to-peer support.Contact form: participants can ask questions and receive feedback from a psychologist via email. If required, the participant is referred to professional care. Technical assistance is also provided.“My Psyfit”: the participant can download and print out a personal PDF blueprint of the intervention with all the modules, exercises, and progress measurements completed.Videos: each module starts with a video showing a Dutch expert explaining the relevance of this particular module.Module self-tests: each module starts and ends with a short self-test to see if the particular skill has improved.

The participant can work through the intervention independently (self-help) but can fill in a contact form with a question if necessary. Psyfit could be likened to a toolbox from which people can “pick and mix” whatever they like and need. The web statistics module will systematically track and trace the actions of each participant, such as the number of log-on times, the time spent on the website, and the modules chosen. This enables adherence to the intervention to be examined.

**Figure 1 figure1:**
[figure not shown]
Screenshot of the Psyfit portal.

### Control Group

Participants in the control condition are placed on a waiting list for 6 months. After a 6-month follow-up assessment, they will receive their personal user name and password for Psyfit.

### Assessments

The primary outcome measure is well-being. Secondary outcome measures include depressive symptoms, general health and vitality, and economic costs (as measured by health care use, days of absence, inefficient job performance, and work productivity). For an overview of outcomes and instruments, see Table 1.

Measurements will be taken at baseline (pre-test), directly after the intervention (post-test, 2 months after baseline), and 6 months later (follow-up). All measurements are self-report measures and will be administered via email with a link to the questionnaire on the Internet.

High dropout rates are a characteristic feature of online trials and can be as high as 50% [50]. Therefore, email reminders and rewards (eg, raffle of six iPods and vouchers) for filling in the questionnaires will be used. It is expected that this will lead to a lower attrition rate.

**Table 1 table1:** Questionnaires and assessment times.

		T0	T1	T2
Questionnaire^a^	Measurement	Pre-test	Post-test^b^	Follow-up^c^
MHC-SF	Well-being/positive mental health	X	X	X
WHO-5	Well-being	X	X	X
CES-D	Symptoms of depression	X	X	X
MOS SF-36 subscales	Vitality and general health	X	X	X
TIC-P and PRODISQ	Health service uptake and production losses	X	X	X
CSQ-8	Client satisfaction		X	
Demographics	Age, gender, education, marital status, job status	X		

^a ^all questionnaires are discussed within Instruments section

^b ^2 months after T0

^c ^6 months after T0

### Instruments

#### Well-Being and Positive Mental Health

Well-being will be assessed with two questionnaires measuring different concepts. The Mental Health Continuum-Short Form (MHC-SF) [51] is a 14-item self-report questionnaire that categorizes measures of well-being as “languishing,” “moderate,” or “flourishing.” Participants rate the items on a 6-point scale from 0 (never) to 5 (every day). The MHC-SF measures subjective well-being as well as psychological and social well-being. These aspects are all addressed in Psyfit; therefore, this questionnaire was chosen. The MHC-SF has shown good internal consistency (> .80) and discriminant validity [44,52].

The WHO-Five Well-being Index (WHO-5) contains 5 positively formulated items on mental health [53]. Participants are asked to rate the items using a 6-point scale ranging from 0 (never) to 5 (all of the time). The WHO-5 has been validated in different populations [53] and is useful as a screening instrument for depression [54]. It was chosen as a measurement instrument because of its brevity and the concurrent validity with depression.

#### Depressive Symptoms

Depressive symptoms will be measured by the Dutch version of the Center for Epidemiological Studies Depression Scale, the CES-D [55]. The CES-D is a 20-item self-rating scale with item scores ranging from 0 to 3 (higher scores indicating more depression), and a total score from 0 to 60. The CES-D has acceptable reliability and validity with a cut-off score of 16 for mild depressive symptoms [42] and a cut-off score of 25 for severe depressive symptoms [56]. When applied via the Internet, the CES-D appears to be a reliable and valid instrument [45].

#### Vitality and General Health

Two quality of life related constructs, “vitality” and “general physical health” will be measured with two scales from the Medical Outcomes Study Short Form-36 (MOS SF-36) [57]. The vitality subscale contains 4 items which are rated on a 4-point scale ranging from 1 (all the time) to 6 (never). The “perception of general health” subscale consists of 5 items which are rated on a 5-point Likert scale (1 = “exactly right” to 5 = “exactly wrong”). The MOS SF-36 has demonstrated good reliability and validity [58].

#### Economic Costs

The economic evaluation will be conducted from a societal perspective. It includes utilization costs of any type of health care and medicines (direct medical costs), costs incurred by the participants for travel and parking (direct non-medical costs), and costs due to production losses (indirect non-medical costs) [59,60]. All costs will be expressed in Euro (€) on an annual per capita basis for the reference year 2010. Data on direct medical and non-medical costs are obtained by using the Dutch Cost Questionnaire for Psychiatry (TIC-P) [59]. Six items from the Productivity and Disease Questionnaire (PRODISQ) will be used to measure indirect non-medical costs [61] stemming from productivity losses due to days of absence and presenteeism/inefficient job performance.

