The economic evaluation will be conducted from a societal perspective, thus including the intervention costs (ie, Psyfit), the costs of health care uptake (TIC-P), the participants’ out-of-pocket costs for obtaining health care (TIC-P), and the economic costs due to productivity losses in paid work (PRODISQ). The incremental cost-effectiveness ratio (ICER) will be calculated. Uncertainty in the ICER will be captured using a bootstrap approach, producing a scatter of simulated ICERs over the ICER-plane and by drawing an ICER acceptability curve of the likelihood that Psyfit is more cost-effective for a range of willingness-to-pay (WTP) ceilings.

All analyses will be conducted using two-sided tests and alphas of .05. For this purpose, the most recent version of the SPSS software will be used.

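### All costs are put on an annual basis, although the randomised comparison and the last cost and effect data end at 6 months

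*Protocol article*

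**What the plan says.** The Economic Costs section sets one time basis for every cost: all are to be given in euros "on an annual per capita basis for the reference year 2010". No other cost basis appears in the article.

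The comparison itself is shorter. Under Study Design, control "participants will be put on a waiting list for 6 months before they are offered access to Psyfit", and under Control Group, "After a 6-month follow-up assessment, they will receive their personal user name and password for Psyfit". Table 1 schedules the outcome scales and the cost questionnaires (TIC-P and PRODISQ) at T0, T1 and T2, and its footnote places T2 "6 months after T0". The Methods paragraph of the Abstract agrees.

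The running text under Assessments is looser: "directly after the intervention (post-test, 2 months after baseline), and 6 months later (follow-up". Taken alone, that could mean 6 months after post-test, but Table 1 and the Abstract settle it at 6 months from baseline. Either reading falls short of a year.

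On the ratio, the Analysis section says only that "The incremental cost-effectiveness ratio (ICER) will be calculated", with a bootstrap for its uncertainty and an acceptability curve over a range of willingness-to-pay ceilings. It names neither a time horizon nor an effect unit, and does not say how 6-month data become annual costs.

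**The concern.** Once controls receive Psyfit there is no untreated arm to compare with, and nothing is measured after T2. A 12-month cost difference between the arms therefore cannot be observed in this trial. It can only be projected from the first 6 months.

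An ICER is interpretable only if its cost difference and its effect difference refer to the same period. The article fixes the costs at a year, while every effect measure ends at 6 months. The Psyfit cost adds a further difficulty: it arises once, for a single 2-month access period, so it has no natural annual rate. At stake are the ICER, its bootstrap scatter and the acceptability curve, which are the main results of the economic evaluation.

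**Working it through.** The economic text contains no computed figure, so there is none to reproduce. The check is of what the stated cost basis does to the ratio.

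**Inputs from the protocol article**
- Cost basis: 12 months (Economic Costs).
- Randomised comparison: 6 months (Study Design, Control Group).
- Last cost and effect measurement: 6 months after baseline (Table 1, Abstract).
- Psyfit access: one period of 2 months (Study Design), so its cost arises once.

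**Inputs not in the documents (assumed, for illustration only)**
- E = 0.15, the effect difference at 6 months, taken as a difference in the proportion responding.
- I = 50, 100 or 300 euros, the one-off Psyfit cost per participant.
- D = −200, −75 or +200 euros, the 6-month difference in all other costs (Psyfit minus control; negative means savings).

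**Step 1: scaling factor.** Linear annualisation multiplies 6-month costs by 12/6 = 2.

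**Step 2: the ratio under each rule.**
- Common 6-month horizon: (D + I)/E.
- All costs annualised over the 6-month effect: 2(D + I)/E, exactly twice the first.
- All except the one-off cost annualised: (2D + I)/E, which differs from the first by D/E.

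**Step 3: when the sign changes.** Doubling everything never changes the sign. With the one-off cost unscaled, the sign changes when D + I > 0 and 2D + I < 0, that is, when −I < D < −I/2. In words, 6-month savings must exceed half the Psyfit cost but not reach all of it. The reverse change is impossible: if D + I < 0, then 2D + I < 0 as well.

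**Step 4: numbers (euros per unit of effect, E = 0.15).**

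| I | D | 6-month horizon | All scaled | One-off cost unscaled |
|---|---|---|---|---|
| 50 | −200 | −1,000 | −2,000 | −2,333 |
| 50 | −75 | −167 | −333 | −667 |
| 50 | +200 | 1,667 | 3,333 | 3,000 |
| 100 | −200 | −667 | −1,333 | −2,000 |
| 100 | −75 | 167 | 333 | −333 |
| 100 | +200 | 2,000 | 4,000 | 3,333 |
| 300 | −200 | 667 | 1,333 | −667 |
| 300 | −75 | 1,500 | 3,000 | 1,000 |
| 300 | +200 | 3,333 | 6,667 | 4,667 |

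For example, with I = 100 and D = +200: (200 + 100)/0.15 = 2,000; 2 × 300/0.15 = 4,000; (400 + 100)/0.15 = 3,333. The sign changes in two of the nine rows (I = 100 with D = −75, and I = 300 with D = −200), the two that fall inside the window in Step 3.

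**Step 5: acceptability curve.** Let C be the 6-month total cost difference and W the willingness-to-pay ceiling. With all costs doubled, the curve at W is the probability that W·E − 2C > 0. This equals the probability that (W/2)·E − C > 0, which is the 6-month curve at W/2. Every ceiling is therefore misread by a factor of two. With the one-off cost unscaled, the shift is not a simple rescaling of the axis.

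**Step 6: direction.** With D > 0, both annual rules raise the ICER, against Psyfit. With D < 0 and the one-off cost unscaled, the ratio falls, in favour of Psyfit. With all costs scaled and D + I < 0, the apparent saving doubles, also in its favour.

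**The case against.** The strongest reply is that the Economic Costs section only fixes a unit of expression. Annual per capita could mean a rate in euros per person-year, which assumes nothing about months 7 to 12, and the Analysis section never says that these figures enter the ICER over a 6-month effect. This stands in part: the mixing of horizons is an inference, not written text. But the annual basis is the only one given, it covers all costs, and no effect is measured after 6 months. A rate per person-year divided by a 6-month effect also carries the factor of two.

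A second reply is that a condensed article may leave the ICER horizon to a fuller document. That is fair, and the missing horizon is not itself the point. The point is the annual basis, which is stated.

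Third, the Current Study section makes the economic evaluation a secondary objective, and the efficacy comparison is untouched. That stands and limits the weight of the point.

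Three stronger readings are tempting, and the documents do not support them:
- A reader might infer that annualising turns a net cost into a net saving. This needs the one-off cost to be left unscaled, a rule the article does not state, and savings inside the window in Step 3.
- A reader might infer that the choice flatters Psyfit. The distortion runs either way.
- A reader might infer that participant time is wrongly left out of the societal costs, since the article says of module work: "On average, this takes 20 to 30 minutes each day". The Analysis section includes Psyfit intervention costs without defining their components, itemised costing is commonly left to a fuller document, and the valuation of leisure time is debated. Exclusion is not established, and the matter forms no part of this point.

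**Conclusion.** The point holds as an inconsistency between a stated cost basis and the period the trial can compare. Annual costs here are an unlabelled extrapolation. If they enter the ICER with the 6-month effect, and scaling is linear, the ICER is doubled and the acceptability curve is shifted by a factor of two when all costs are scaled. If the Psyfit cost is not scaled, the ICER moves by D/E, with a change of sign only when 6-month savings lie between half and all of that cost.

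The factor of two rests on the documents' 6 and 12 months and on linear scaling. The euro figures rest on assumed values and show only the pattern. No direction of bias can be claimed in advance. The economic result is affected; the primary efficacy result is not. The authors should correct this before analysis.

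**What to change.** State in the Analysis section that the ICER, the bootstrap and the acceptability curve use cumulative costs per participant from T0 to T2, in 2010 euros, with the Psyfit cost counted once, paired with the effect at T2. In the Economic Costs section, keep the 2010 reference year and replace the annual basis with the 6-month one. If an annual figure is wanted, show it separately as an extrapolation and state its assumptions, including how the one-off cost is treated.

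This is a change of wording, with no new assessments. The one cost concerns coverage: the article does not give the recall windows of the TIC-P and PRODISQ. If these do not cover all 6 months, cumulative costs will need some interpolation between T0, T1 and T2, and the method should be stated.
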